### Sample size

The sample size calculation for this study is based on index data from the Toledo Healthy Aging Study. Since the prevalence rates of frailty, as well as the progression of frailty syndrome, are expected to be higher in the clinical population than in the general population, these estimates can be considered conservative and therefore offer an additional safety margin to achieve sufficient statistical power.

Frailty rates are estimated from subjects who have a negative FTS5 that later develop frailty, which was 0.075 (7.5%). The ratio of exposed/ unexposed was 1008/196 (ratio of negatives vs. positives), that is 5.1. The minimum relative risk value (RR) to be detected is estimated taking as an interest variable “incident frailty” (stage transition marker) for which OR of the different estimates range between 1.78 and 5.4 and therefore we adopt a RR conservative to detect of 2. Finally, the loss of follow-up rates is estimated at 10%.

With these data, sample size was calculated using a Poisson distribution approach, appropriate for the analysis of event rates. The calculation was based on the expected incidence rate of the outcome, the anticipated rate ratio between groups, a two-sided significance level of 0.05, and a statistical power of 80%. Therefore, accepting an Type 1 error of 0.05 and a Type II error of 0.2 in a two-sided contrast, 215 subjects in the exposed group and 1075 in the unexposed group are needed to detect a factor of risk with a minimum relative risk value of 2.

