Finally, the identified frailty phenotypes and patient clusters will be examined in relation to clinically relevant health outcomes, including the utilization of health care services in both primary and secondary care settings, hospital admissions, biomarker profiles, and mortality. Appropriate regression models will be used depending on the outcome of interest, and results will be reported using effect estimates with corresponding 95% confidence intervals. Where applicable, analyses will account for follow-up time and relevant covariates. These analyses will enable the assessment of the prognostic and clinical relevance of the identified frailty phenotypes and trajectories.

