In summary, the project aims to advance our understanding of the interindividual variability in clinical trajectories that lead to frailty, dependence, and eventually, death. Specifically, this proposal will:

Enable early detection of individuals at risk of progressing to frailty and dependence by identifying characteristic phenotypic profiles.Facilitate longitudinal monitoring of frailty progression and vulnerability in individual patients based on defined risk pathways.Support the definition of standardized, well-characterized populations in which preventive or therapeutic interventions can be tested.Provide a framework for the identification of homogeneous clinical clusters suitable for clinical and epidemiological research.Lay the groundwork for future studies on biological markers related to the progression of frailty and vulnerability.

The overarching goal of the project is to minimize the impact of frailty and its consequences—particularly dependence—by improving diagnostic classification, prognostic evaluation, and the development of tailored management strategies for distinct risk phenotypes.

The results will be continuously disseminated to the scientific and medical community via meetings with other researchers, clinical sessions, and patient associations. Upon completion of the study, the findings will be published in peer-reviewed journals.

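### The stated measure of prognostic relevance is group effect estimates, and trajectory classes use the whole follow-up; neither establishes the early detection of individuals that the Discussion claims

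*Protocol article*

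**What the plan says.** The last paragraph of the Statistical analysis plan section relates the identified phenotypes and patient clusters to service use, hospital admissions, biomarker profiles and mortality. Regression models are to be chosen by outcome, and "results will be reported using effect estimates with corresponding 95% confidence intervals". The paragraph closes with what is to follow from this: "These analyses will enable the assessment of the prognostic and clinical relevance of the identified frailty phenotypes and trajectories".

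The paragraph before it says how the trajectory classes arise. Deficits are recorded until follow-up ends, the participant dies or is lost, and latent trajectory models then assign participants to classes. Under Secondary variables, health-care use and non-elective admissions are counted over the study period.

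The Discussion's summary list says that the project will "Enable early detection of individuals at risk of progressing to frailty and dependence by identifying characteristic phenotypic profiles". A further item promises monitoring of progression in individual patients.

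The Sample size section supplies figures for an illustration: 7.5% incident frailty among FTS5 negatives, 1008 negatives and 196 positives, and, for the effect, "OR of the different estimates range between 1.78 and 5.4", from which "therefore we adopt a RR conservative to detect of 2".

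**The concern.** Two steps in the reasoning do not hold as written.

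First, an effect estimate compares average risk between groups. Early detection of individuals depends on how many future cases fall in the flagged group, and on how many flagged people become cases. A ratio that is clearly different from 1 is compatible with poor performance on both counts.

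Second, a trajectory class is known only once the decline has been observed. Relating it to admissions and deaths from the same period describes what went together. It does not show what could have been foreseen at V0.

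At stake is the conclusion on individuals. The cohort, the clustering and the regressions remain valid as group-level work. If the plan is followed as stated, though, the claim about individual patients would be published without an analysis that supports it.

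**Working it through.** **The plan's own figure.** Inputs from the Sample size section: risk 0.075 in the unexposed, relative risk 2 (so 0.15 in the exposed), about 5 unexposed per exposed, two-sided 0.05, power 80%, 10% loss. The unpooled two-proportion formula gives

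n(exposed) = (1.96 + 0.84)² × [0.15 × 0.85 + 0.075 × 0.925 / 5] / (0.075)² ≈ 197.3, so 198.

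Allowing for loss gives 198 / 0.9 = 220, or 198 × 1.1 ≈ 218. Both are within 3% of the stated 215 exposed (with 1,075 unexposed), so the inputs are read as the authors meant them. The section names a Poisson approach. The Poisson forms tried gave 170 to 257 after loss, and none was within 3% of 215. The present point does not depend on this.

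**What a relative risk of 2 looks like as a group result.** At 215/1,075 the expected events are 215 × 0.15 = 32.25 and 1,075 × 0.075 = 80.6. SE(log RR) = √(1/32.25 + 1/80.6) = 0.208. The 95% interval is 2 × exp(±1.96 × 0.208), about 1.33 to 3.01 before loss.

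**The same effect as individual detection.** Take FTS5 positive as the flag, with 196 flagged of 1,204 (16.3%).

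- Cases among flagged: 196 × 0.15 = 29.4. Cases among unflagged: 1008 × 0.075 = 75.6. Total 105.
- Sensitivity = 29.4 / 105 = 28.0%, so 72.0% of cases are unflagged.
- Specificity = 932.4 / (932.4 + 166.6) = 84.8%.
- Positive predictive value = 15%.
- AUC of a binary flag = (sensitivity + specificity) / 2 = 0.564.

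**Across the plan's range.** An odds ratio is converted by p1 = OR × 0.0811 / (1 + OR × 0.0811), where 0.0811 = 0.075 / 0.925.

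| Effect | Risk if flagged (= PPV) | Sensitivity | Cases unflagged | Specificity | AUC |
|---|---|---|---|---|---|
| OR 1.78 | 12.6% | 24.6% | 75% | 84.5% | 0.55 |
| RR 2 | 15.0% | 28.0% | 72% | 84.8% | 0.56 |
| OR 5.4 | 30.5% | 44.1% | 56% | 87.2% | 0.66 |

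Reading 5.4 as a relative risk gives 49% unflagged and AUC 0.70. Using the planned 215/1,075 split at RR 2 gives 71.4% and 0.565.

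**A labelling point.** The section writes "The ratio of exposed/ unexposed was 1008/196 (ratio of negatives vs. positives), that is 5.1", which puts the negatives in the exposed position. The final 215 exposed and 1,075 unexposed fit the opposite reading, which is used here. The literal label would leave 9% of cases unflagged at RR 2, but with most people flagged, and the AUC would still be only 0.54.

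**Trajectory classes.** No arithmetic is needed. The classes use deficits up to the end of follow-up, death or loss. Admissions and health-care use are counted over the study period. Predictor and outcome share one window, and the article states no step that predicts class membership from V0.

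**The case against.** Several points on the other side stand.

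- **The measure is not said to be the only one.** A reader might infer that no accuracy measure will be reported. The article does not exclude one, and a full protocol or analysis plan, not shown, may specify it. The absence of AUC from an article is not in itself an error.
- **The numbers are not about the clusters.** A reader might infer that the study's phenotypes will miss 72% of those who become frail. The documents do not support that. The figure comes from the FTS5 split with incident frailty. The final analysis step concerns clusters and trajectories, and its outcome list does not name incident frailty. The Main variables section treats an FTS5 score above 25 as frailty already present, so the split is not a phenotype that the plan proposes as a risk flag. Relative risk 2 is also the minimum to detect, not the expected effect.
- **There is no stated decision rule.** A reader might infer that an interval excluding 1 would count as prognostic relevance. The article sets no such threshold.
- **The clustering is unsupervised.** It does not use the later outcomes, so the optimism of a fitted prediction model does not carry over directly. The plan also says that the robustness of cluster assignments will be assessed.
- **The individual-level claim sits in the Discussion.** The stated overall goal is to identify subgroups at risk, which group-level analysis fits.

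None of this closes the gap between the two published statements. The article says what its analyses will establish and then claims more for individuals. The gap statistic and silhouette index describe the clusters, not prediction, and the three frailty scales are only said to be compared with each other. The timing problem with trajectory classes is independent of all the figures.

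**Conclusion.** The point holds in a limited form. Group effect estimates, the measure stated for prognostic relevance, do not establish early detection or monitoring of individuals. Trajectory classes cannot be called prognostic when they are built from the same period as the outcomes.

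The size is illustrative: AUC about 0.55 to 0.66, with 75% to 56% of cases unflagged, over the plan's own odds ratio range. This assumes a two-group flag with the FTS5 split, 7.5% risk in the unflagged, FTS5 positives as the exposed group, and incident frailty as the outcome. A phenotype with several classes could do better or worse. The illustration shows that an effect the study is sized to detect can separate individuals poorly; it does not say that this study's phenotypes will.

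This is an inexpensive improvement that changes what the study can conclude. It is not a flaw in the cohort or in the regressions.

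**What to change.** In the last paragraph of the Statistical analysis plan section:

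1. For phenotypes assigned from V0 data, report the AUC or C-statistic, sensitivity and positive predictive value beside each effect estimate. Do so at V1 and V2 for incident frailty (among those not frail at V0), non-elective admission and death. V2 should be qualified by available follow-up, because the Study schedule section gives both a one-year minimum and a minimum of three visits.
2. Obtain these figures with internal validation, for example by bootstrap or by applying a fixed cluster assignment rule across centres. Re-forming the clusters in each subset of centres is less suitable, since their number and meaning may change.
3. Relate trajectory classes to outcomes descriptively, unless class membership is predicted from V0 data.
4. In the Discussion, rest the early-detection and individual-monitoring claims on these figures, or limit them to group-level association.

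The cost is wording and modest extra analysis, with no new visits, data or staff. The Gantt chart dates data analysis from January 2028 and marks it pending, so the change can be fixed in advance. The downside is that the reported performance will look less favourable than the ratios.

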### Data collection and management

We use a data collection platform (REDCAP) designed by Hospital Universitario de Getafe, accessible to all project researchers. Participant identification is encoded at the time of inclusion in REDCAP. The project’s principal investigator (PI) can export REDCAP data to various applications (Excel, SPSS, etc.). The coordinating researchers will manage the anonymized data for project analyses and data confidentialy. Data will be validated by PI and statistical researchers.

### Potential bias

All centers involved in participant recruitment have a specific outpatient clinic focused on frailty and the management of older adults. These centers are geographically distributed throughout Spain, minimizing potential bias.

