## Abstract

Frailty has become a major challenge for health systems, but it also presents a window of opportunity to fight disability through preventive strategies focused on the detection and treatment of frailty across all care settings. However, no systematic strategies for screening and early detection are currently available in clinical practice. This project aims to identify clinical and biological phenotypic clusters that drive progression through the different stages of frailty, and to describe the underlying mechanisms of the trajectories leading to disability and potential treatment interventions. In addition, the Frailty Trait Scale 5 (FTS5) will be validated as a practical tool for implementation in both primary care and hospital settings. A prospective, population-based cohort (CohorFES) will be established for frailty phenotyping. A CIBERFES Biobank will also be created to store blood and urine samples from CohorFES participants for future research. Demographic and clinical history data, anthropometric measurements, the PREDIMED questionnaire, peripheral blood biochemical variables, and metabolomics data will be collected at baseline and annually until participants develop frailty. Cluster partition models (k-means and hierarchical clustering) will be used to group individuals with similar deficits and characteristics (frailty phenotypes). Then, by using pre-established criteria (gap and silhouette), the proposed clustering solution (belonging to given clusters) will be evaluated. We will also assess, in a longitudinal manner, the emergence and accumulation of deficits over time, identifying subgroups with more rapid progression. The results will be used to define and compare clusters and progression trajectories. Finally, frailty phenotypes and patient clusters will be correlated with health outcomes such as healthcare utilization (primary and secondary care), hospital admissions, and mortality. Information on clinical and biological phenotypic clusters involved in the progression of frailty may help identify potential therapeutic targets to improve the management of these patients. In summary, from a research perspective, this project aims to improve our understanding of the interindividual variability in clinical trajectories that lead to frailty, dependence, and ultimately, death.

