With this in mind, a shorter version comprising only 5 items (the so-called FTS5) was developed [12]. This version offers promising results, maintaining the sensitivity to detect small changes shown by the full FTS. The variables that make up the FTS5 (gait velocity, grip strength, BMI, PASE, and balance) can also be incorporated into electronic tools, such as the electronic frailty index (eFI) [13]. The use of such electronic tools has proven useful not only in hospital care but also in routine primary care practice. Furthermore, it facilitates the measurement of adverse outcomes, including falls, delirium, disability, care home admission, hospitalization, and mortality, as recently demonstrated [14].

In this regard, several clinical guidelines have been proposed for the early identification and prevention of frailty in the elderly [15–17]. These guidelines aim to address one of the major healthcare challenges: the growing aging population and the increasing incidence of chronic diseases. In particular, in 2022, the Frailty and Falls Prevention Working Group updated a “consensus document on the prevention of frailty in the elderly,” approved by the Interterritorial Council of the Spanish National Health System. This document highlights the importance of early diagnosis and the need for interventions within the healthcare system, especially in primary care [15]. This aspect is particularly important because frailty is not an inevitable consequence of aging; instead, it represents a dynamic and potentially reversible condition, with early stages offering the greatest opportunity for recovery.Therefore, early detection and diagnosis of frailty are essential not only for quality of life but also for the efficient use of healthcare and social resources.

Our overarching goal is to identify critical subgroups of individuals at risk of progressing from robustness to pre-frailty and frailty, and from there to later stages, as well as the pathways mediating this trajectory in community-dwelling Spanish subjects.

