Within this conceptual framework, and considering the limited data available in clinical settings regarding frailty diagnosis, trajectories, and prognosis, the main goal of this project is to establish a real-life, clinical, prospective cohort (CohorFES). This cohort aims to identify clinical and biological phenotypic clusters contributing to progression through the different stages of frailty and to elucidate the underlying mechanisms that ultimately lead to disability.

Additionally, the project will validate the Frailty Trait Scale 5 (FTS5) as a practical and easily applicable tool for use in both primary care and hospital settings.

Finally, a multicenter biobank will be created within the CIBERFES consortium to store blood and urine samples from CohorFES participants, ensuring their availability for future research initiatives.

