## Materials and methods

### Study design and setting

We will stablish a multicentered cohort, the CohorFES, a prospective and observational study based on population. The study is registered in clinicaltrials.Gov as observational study: NCT06965972 (date 05/02/2025). Patients will be recruited from the start of the project and will be followed annually throughout the study.

Participants are women and men over 65 years old who attend outpatient clinics at participating centers, including the Hospital del Mar Research Institute in Barcelona, the Hospital General Universitario Gregorio Marañón in Madrid, the Complejo Hospitalario Universitario de Albacete in Albacete, the Hospital General Universitario de Ciudad Real in Ciudad Real, the Fundación del Hospital Nacional de Parapléjicos in Toledo, and the Hospital Universitario de Getafe in Madrid.

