#### Main variables.

The main variables are based on the evaluation of the frailty score:

**Frailty Trait Scale 5 items (FTS5**): 1.- walking speed test, 2.- grip strength, 3.- Physical Activity, 4- Body Mass Index (BMI), and 5.- progressive Romberg test. Each of the 5 domains scores from 0 (the lowest) to 10 (the highest), being 50 the highest score possible in this tool. Participants with a score higher than 25 were considered as frail [12].**Fried phenotype**: 1.-weight loss, 2.-exhaustion, 3.-weakness, slowness, and 4.-low physical activity. Frailty status was defined as robust or nonfrail (individuals who did not meet any criteria), prefrail (1 or 2 criteria met), and frail (≥3) [7].**Electronic Frailty index (eFI):** It is a validated instrument that operationalizes the cumulative deficit model of frailty, using routinely collected electronic health record data (36 items) to quantify frailty and stratify older adults according to their risk of adverse outcomes such as hospitalization, institutionalization, and mortality [13].

These three frailty parameters will be compared to each other to validate whether the FTS5 could be used as a practical and easy-to-apply tool in both primary care and hospital settings.

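### CohorFES is labelled population-based but enrols hospital-clinic attenders; geographic spread does not remove that selection, and the primary-care half of the FTS5 validation aim is unsupported

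*Protocol article*

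**What the plan says.** The article describes the cohort in two ways. The Abstract states: "A prospective, population-based cohort (CohorFES) will be established for frailty phenotyping". Study design and setting repeats the label: "a prospective and observational study based on population". The Introduction, however, gives the main goal as to "establish a real-life, clinical, prospective cohort (CohorFES", while its overarching goal concerns "the pathways mediating this trajectory in community-dwelling Spanish subjects".

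Under Study design and setting and Sampling procedure, participants are people over 65 who come to outpatient clinics at the participating centres and are invited consecutively. Six centres are named; each is a hospital or a hospital-linked institute or foundation. The Potential bias section adds: "All centers involved in participant recruitment have a specific outpatient clinic focused on frailty and the management of older adults". It then concludes: "These centers are geographically distributed throughout Spain, minimizing potential bias".

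FTS5 is to be validated "as a practical and easily applicable tool for use in both primary care and hospital settings"; the Abstract, Main variables and Discussion repeat this aim. Main variables states the method: "These three frailty parameters will be compared to each other to validate whether the FTS5 could be used". The three measures are FTS5, the Fried phenotype and the electronic Frailty Index (eFI). The Limitations section names recruitment coordination, with data homogeneity and sample size, and does not mention selection.

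**The concern.** A population-based cohort draws on a defined population, so that its prevalence, cluster sizes and transition rates describe that population. Consecutive enrolment of clinic attenders does not do this. If the label stays, readers may take the frailty phenotypes and progression rates as estimates for older people in Spain generally.

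The bias sentence makes this worse, because it offers geographic spread as the remedy for a selection that spread does not touch. For FTS5, the stated conclusion reaches a setting, primary care, in which no recruitment is described. Agreement between scales and predictive performance can both depend on the mix and frequency of frailty among the people studied. Results from hospital outpatients therefore cannot be assumed to carry over.

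**Working it through.** The point rests on no figure in the article, so the check sets the statements side by side.

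1. **Label against sampling.** The label is population-based (Abstract; Study design and setting). The sampling is consecutive invitation of attenders at outpatient clinics (Study design and setting; Sampling procedure). No population register, catchment sample or other population frame is described. The Introduction's word clinical fits the sampling; the label does not.

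2. **Does the article expect the clinic population to differ?** Yes. The Sample size section takes its inputs from the Toledo Healthy Aging Study and calls them conservative, because frailty prevalence and progression should both be higher in a clinical population than in a general one. The same document therefore relies on the difference for its sample size and passes over it in its bias statement.

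3. **What geographic spread can do.** Let the difference between a centre's attenders and the older population be a regional part plus a part due to attending such a clinic. Averaging over centres can reduce the regional part. The attendance part is present at every centre, and its average over centres is not zero, however many regions are covered. The sentence just before the bias claim describes such a shared feature: every recruiting centre runs a frailty or older-adult clinic. The spread is also modest. Of the six named centres, two are in Madrid (counting Getafe, as the article does), one each in Toledo, Ciudad Real and Albacete, and one in Barcelona.

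4. **Primary care.** The aim names two settings. The described recruitment covers hospital outpatients. The list of centres is introduced as non-exhaustive, so unnamed sites are possible, but the Potential bias section says that all recruiting centres have the specialised outpatient clinic. Nothing in the article describes enrolment through primary care.

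5. **Overlap between the scales.** The FTS5 items in Main variables are walking speed, grip strength, physical activity, BMI and a progressive Romberg test. The Fried criteria are weight loss, exhaustion, weakness, slowness and low physical activity. Walking speed pairs with slowness, grip strength with weakness, and physical activity with low physical activity. That is three of five domains on each side, so some agreement between FTS5 and Fried is to be expected whether or not FTS5 predicts outcomes. The eFI uses 36 items from electronic health records, so this overlap argument does not clearly apply to it.

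6. **Outcomes available.** Secondary variables already include all-cause mortality, non-elective admissions and the Barthel Index. The analysis plan relates phenotypes and clusters to health outcomes, but does not name FTS5 as a predictor there.

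**The case against.** Several points on the other side stand.

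- **Only frailty clinics, or only referred patients.** A reader might infer either. The article says that each centre has such a clinic, not that recruitment is confined to it, and it describes no referral route. The argument needs neither, because it applies to any hospital outpatient clinic.
- **The whole FTS5 aim fails.** A reader might infer this too. The hospital-outpatient part is sound, and the Introduction names the shortage of data from clinical settings as the gap to fill. Clinic-derived clusters and trajectories serve that purpose.
- **The exclusions.** Leaving out people hospitalised in the previous six months, with a Barthel score below 60 or at the end of life removes sicker patients. This may bring the cohort closer to community-dwelling older adults. The net difference is unknown, although the Sample size section still expects higher frailty rates.
- **Circular validation.** Three shared domains do not guarantee agreement. FTS5 is a 0 to 50 score with its own cut-off, it includes BMI and balance, and it omits exhaustion and weight loss. The eFI is a third comparator. The sample size calculation itself rests on an FTS5-positive versus FTS5-negative contrast for incident frailty, with a relative risk of 2 to be detected, so some prospective assessment of FTS5 is built in. The article does not say which scale defines incident frailty.
- **Validation metrics.** A condensed article may leave these to the full protocol. Their absence is no error, and the added analysis proposed here is an improvement.

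None of this reconciles the label with the sampling, makes geographic spread a remedy for attendance selection, or supplies primary-care participants.

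**Conclusion.** The concern holds on three counts. The population-based label contradicts the described sampling and the article's own term clinical. The claim that geographic distribution minimises bias is unsupported, and clinic selection is missing from the stated limitations. The primary-care half of the FTS5 aim has no described recruitment behind it.

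No size can be put on the shift. The article gives no frailty prevalence for CohorFES or for primary care, and no sensitivity or specificity for FTS5. Any contrast in predictive values would rest on assumed inputs and would show dependence on prevalence, not spectrum bias. Only the direction can be taken from the article: more frailty and more progression than in the general population.

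The conclusion assumes that the described recruitment is complete. If primary-care sites do enrol, the third count falls, and the article should say so. A reader might go further and call the cohort unfit for its purpose or the validation worthless. The document does not support that, since inference to hospital outpatients is intact and eFI and outcome data are available.

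**What to change.** - Describe CohorFES throughout as a multicentre hospital-outpatient cohort. Delete or qualify the population-based label in the Abstract and in Study design and setting, and bring the community-dwelling wording of the overarching goal into line.
- Delete the claim in Potential bias that spread minimises bias, or limit it to regional differences.
- Add clinic selection to Limitations, citing the article's own expectation of higher frailty rates.
- Restrict the FTS5 conclusion to hospital outpatients in the Abstract, Introduction, Main variables and Discussion, and state that use in primary care needs external validation.
- Alongside agreement between the scales, report the predictive accuracy of FTS5, Fried and eFI for mortality, non-elective admission and Barthel decline.

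The cost is a narrower claim, some rewording and a little more analysis, with no new data collection. The timing is good: recruitment runs to the end of 2027, and 500 of the planned 1,500 participants have been enrolled.
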